## Abstract

**Background:**

Intimate partner abuse (IPA) is a major public health problem with serious implications for the physical and psychosocial wellbeing of women, particularly women of child-bearing age. It is a common, hidden problem in general practice and has been under-researched in this setting. Opportunities for early intervention and support in primary care need to be investigated given the frequency of contact women have with general practice. Despite the high prevalence and health consequences of abuse, there is insufficient evidence for screening in primary care settings. Furthermore, there is little rigorous evidence to guide general practitioners (GPs) in responding to women identified as experiencing partner abuse. This paper describes the design of a trial of a general practice-based intervention consisting of screening for fear of partner with feedback to GPs, training for GPs, brief counselling for women and minimal practice organisational change. It examines the effect on women's quality of life, mental health and safety behaviours.

**Methods/Design:**

**weave **is a cluster randomised controlled trial involving 40 general practices in Victoria, Australia. Approximately 500 women (16-50 years) seen by the GP in the previous year are mailed a short lifestyle survey containing an item to screen for IPA. Women who indicate that they were afraid of a partner/ex-partner in the last year and provide contact details are invited to participate. Once baseline data are collected, GPs are randomly assigned to either a group involving healthy relationship and responding to IPA training plus inviting women for up to 6 sessions of counselling or to a group involving basic education and usual care for women. Outcomes will be evaluated by postal survey at 6 and 12 months following delivery of the intervention. There will be an economic evaluation, and process evaluation involving interviews with women and GPs, to inform understanding about implementation and outcomes.

**Discussion:**

The **weave **trial responds to an urgent need for more evidence on what can be achieved in primary care with regard to responding to women who experience IPA. It will provide important knowledge about the effectiveness of a brief method of screening, professional IPA training program and brief counselling for women.

**Trail Registration:**

[ACTRN12608000032358]

## Background

Intimate partner abuse (IPA) or violence is defined as any behaviour within an intimate relationship that causes physical, psychological or sexual harm to those in the relationship [1]. Behaviours include acts of physical aggression such as slapping and kicking; psychological abuse such as intimidation and humiliation; forced intercourse and other forms of sexual coercion; and various controlling behaviours such as isolating a person from their family and friends, monitoring their movements, and restricting access to information or assistance. IPA sits within the broader context of gendered violence and the majority of assaults by partners are directed at females [1,2]. Moreover, sexual abuse and partner violence resulting in significant injury are much more commonly perpetrated against women by their partners than against men [3]. Partner abuse is a major public health problem globally. It diminishes women's capacity to participate in occupational, social and familial life and contributes to significant morbidity and mortality among women of child-bearing age [4]. IPA is a complex problem arising from an interplay of personal, situational and socio-cultural factors [2]. Thus, in addition to the need for multifaceted social and educational interventions, early intervention in healthcare settings is required. Primary care offers such an opportunity.

### Prevalence of IPA

Partner abuse is a common but hidden problem for women of child-bearing age. Across ten culturally and economically diverse countries, the World Health Organisation reported the lifetime prevalence of physical and/or sexual partner violence as ranging from 15% to 71% [5]. An Australian general practice study found that almost 30% of women had at some point in their lives been afraid of a partner [6]. A further GP study using the Composite Abuse Scale (CAS) [7] to measure abuse in the previous 12 months reported that 6% of women of child-bearing age had experienced severe combined physical, emotional and/or sexual abuse; a further 7% experienced physical and emotional abuse; 6% experienced physical abuse alone and 6% reported emotional abuse alone [8]. Similarly, a United Kingdom study reported that 17% of women attending general practice had experienced physical violence from a partner/ex-partner in the previous year [9].

### Health consequences of IPA

Partner abuse has been estimated as the leading cause of death and disability among women of child-bearing age [10]. Research consistently highlights a range of severe physical and mental health problems that are associated with partner abuse [4]. Abused women are at increased risk of anxiety, depression, post-traumatic stress disorder, suicide, and drug and alcohol abuse [8,11,12]. Women indicate that the psychological abuse is even more difficult to endure than the physical abuse itself [13]. The most common physical health problems include injuries, chronic pain and gynaecological, cardiovascular, neurological and gastrointestinal problems [14]. Partner abuse may commence, or increase during pregnancy affecting up to 1 in 4 pregnant women [13,15]. In a UK cross-sectional study of women attending general practice, 15% of respondents who had ever been pregnant reported partner violence during pregnancy, with a quarter reporting that this violence was worse than when they were not pregnant and almost one third saying that it had caused a miscarriage [9]. Partner abuse is associated with adverse maternal and infant outcomes e.g. low birth weight [16], foetal injury and pre-term birth [17], and even death of the mother or the foetus [18]. Partner abuse also has associations with common maternal physical health issues - back pain, headache, urinary incontinence and some less common health issues such as bleeding in first trimester, faecal incontinence [19,20]. Partner abuse also has serious consequences for the physical and emotional well-being of children who witness it [21].

### IPA and health care

Abused women are overrepresented in outpatient settings and in primary care [22,23]. Approximately a third of abused women disclose abuse to their GP [24]. Women describe barriers to disclosure that are both internal (e.g. feeling ashamed and embarrassed) and external (e.g. perceiving that doctor is only there for physical problems). GP inquiry is associated with increased disclosure [24], however only 1 in 10 abused women are asked about abuse by the GP [24,25]. Yet there is evidence that women consider it appropriate to be asked about partner abuse [26]. This is moderated by the context of the consultation, the relationship with the health care provider and the woman's readiness to address the problem [27]. Reluctance on the part of health professionals, including GPs, to inquire about abuse owes to factors such as lack of time and training, lack of effective interventions and the complexities of providing whole family care [28,29]. Low levels of inquiry and disclosure have triggered a shift in research focus from studies about prevalence, consequences and patient-health provider interactions to finding improved approaches to screening and intervention.

### Screening

A recent systematic review shows that there is insufficient evidence to justify implementing screening programs [30]. Further support came from a recent Canadian study [31], the first IPA screening trial to examine health outcomes for women. It included 12 primary care sites. The authors concluded that there was not enough evidence to support IPA screening in health care settings as routinely asking all patients in the intervention group about abuse, though not found to be harmful, was no more beneficial in terms of health outcomes than usual care. There was no specific intervention offered to women who were detected by the screening program. Despite women's doctors being informed that they screened positive, half reported that IPA was not raised in subsequent consultations. A major criterion for screening that is not being met relates to the availability of an effective treatment once abuse is identified/disclosed. This means that IPA fails to fulfil public health policy criteria for a screening program in health care settings [30]. There is therefore an urgent need for rigorous testing of specific interventions and services for women following identification of IPA [31,32]. IPA screening instruments are increasingly evaluated against criterion standards such as the Conflict Tactics Scale [33] or Composite Abuse Scale [7]. In a review of 18 brief screening tools in 15 validation studies, Feder et al. found several to be valid for use in health care settings [30]. Inquiring about fear of a partner or ex-partner is receiving increased attention [6,34] and has significant potential as a stand alone screening item. Abused women attending primary care are much more likely (OR = 64.1, 95% CI 44.4-94.1) to have been afraid of a partner or ex-partner at some point in their lives than non-abused women [6]. The fear question has been shown to have good sensitivity and specificity for identifying women who have experienced physical abuse (75.5% sensitivity, 82.4% specificity) or severe combined physical, emotional and sexual abuse (85% sensitivity, 77.7% specificity) in a large sample of women attending GPs for primary care. It does not perform as well in identifying women who have experienced emotional abuse alone (60.6% sensitivity, 80.4% specificity) [7]. It may be concluded that the implementation of screening for IPA is hampered by the absence of evidence for intervention following screening, particularly intervention for women in the early stages of recognising and disclosing abuse. Therefore expanding the evidence base on the optimal method of screening and effective responding is a priority.

### Interventions for women in health care settings

Ramsay et al. reviewed 19 studies to evaluate the effectiveness of health care interventions for women on physical and psychosocial wellbeing and their experiences of abuse [35]. This was recently updated with the addition of 14 studies, 5 of which focused on children for the first time [30]. Studies came from diverse settings (e.g. antenatal clinics, refuges, community settings, primary care) and variously tested the impact of advocacy, support group and psychological (individual or group) interventions on outcomes such as post-traumatic stress disorder, depression, self-esteem and abuse. Overall, the evidence was sufficient to recommend access to advocacy services but this only applied to women who had actively sought help (as opposed to women identified through screening). Evidence for the effectiveness of psychological group therapy, support groups, and child interventions was insufficient on account of too few studies, poor quality design and lack of data for calculating effect sizes. There was sufficient evidence to recommend individual psychological treatments. However, treatments were diverse (e.g. cognitive behavioural therapy, problem-solving, expressive writing, psycho-education, feminist-oriented and grief counselling and forgiveness therapy) and since they largely involved survivors and those actively seeking assistance, they can be extrapolated neither to women identified through screening nor those attending primary care settings. There was a clear absence of qualitative studies examining what women themselves think should be contained in an intervention for IPA [30].

Similar to the absence of women's voices, primary care was under-represented across these studies and settings. The review demonstrates the lack of focus on early intervention and the need for more evidence about woman-centred interventions. While health practitioners are widely encouraged to assume a role in supporting abused women, there are limited guidelines available on how to do this [36]. Most tend to focus on identification and referral rather than on appropriate ways of responding to and counselling women following disclosure. It is imperative to expand the evidence base with respect to the types of counselling that might be effective for abused women who screen positive for abuse. This paper describes the development and design of a trial of screening and intervention in primary care for women who have been afraid of a partner or ex-partner in the last year.

### Evidence informing the development and design of weave

We have outlined in detail [37] the development of the counselling intervention based on the Transtheoretical Model of Behaviour Change [38] adapted to partner abuse [39,40]. We particularly focused on the 'Psychosocial Readiness Model' [41] to conceptualise women's experiences. We used evidence of best practice from systematic reviews of health care-based interventions [30,35] and of qualitative studies with women [27], international primary care guidelines on partner violence [36] and evaluation of general practice-based partner abuse pilots in Australia and overseas. The **weave **brief counselling intervention [37] incorporates motivational interviewing [42] and problem-solving techniques [43], which have been increasingly applied in the primary care setting for depression issues [44]. Finally, partner abuse interventions frequently aim to improve the safety of women [45-47], and this forms a core aspect of our 'Healthy Relationships' training for GPs.

### Outcomes

A key issue in trial design is to identify a set of outcomes that are important to women experiencing abuse and selecting an appropriate means of operationalising these outcomes. Programs focused on women should not be expected to necessarily produce decreased violence in women's lives [48] suggesting that the use of violent events as a primary outcome in trials may be problematic. Change that is internal to the woman is potentially more informative when evaluating the impact of an intervention for partner abuse, especially one that involves direct counselling. Indeed it may be that significant changes in experience of abuse may not be observable for some time after the seeds of change have been sown. Instead it may be more effective to focus on health outcomes for women, such as quality of life and mental health, which have received limited attention in trials to date [31,49]. Emergent areas of measurement include harm - that which potentially emanates from screening, intervention and from participating in IPA research [30].

### Aims of weave

The primary aim of the **weave **study is to determine if a multifaceted intervention consisting of screening for intimate partner abuse and feedback for GPs, training for GPs, a brief counselling intervention for women and minimal practice organisational change results in:

• increased quality of life;

• increased mental health, and;

• increased safety behaviours and planning for women who experience partner abuse.

The secondary aims are to determine if the intervention results in:

• increased readiness for change with regard to the abuse;

• increased comfort on the part of women to discuss partner abuse with GPs;

• increased inquiry by GPs about the safety of women and children;

• reduced anxiety and depression;

and is cost effective.

We hypothesise that the brief counselling intervention will increase women's perceived support and comfort to discuss abuse and lead to positive changes in women's self-efficacy and readiness to change, and that these 'internal' changes will collectively lead to increases in safety planning and behaviours and improvement in mental health and quality of life.

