#### Women

Women will be eligible for the initial screening component of the study if they have consulted the participating GP within the last 12 months and are aged between 16 and 50 years. Women will be excluded if, in exercising clinical judgement, the GP anticipates they may encounter difficulties in providing informed consent, understanding the content of surveys and/or participating in other aspects of the study due to mental or physical health issues, cognitive impairment, intellectual disability or poor English language skills. Additional criteria are required for inclusion in the trial - women will be invited to participate (over the telephone) if they indicate in the screening survey that they have been afraid of their partner or ex-partner in the last 12 months and are interested in hearing more about the **weave **project. Women will be excluded at this stage if it is established during the recruitment phone call that they no longer attend the GP or they are a false-positive. False positives are women who misinterpreted the fear item in that they have never felt afraid of a partner or they have not felt afraid in the previous 12 months.

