### Patient recruitment

Patient recruitment will be done through methods validated in a recent primary care cohort study that screened for probable depression via postal survey, and included a screen for abuse [51]. In **weave**, for each participating GP, a list of female patients, aged 16 to 50 years who consulted the GP at least once in the previous 12 months will be randomly generated (maximum 600 patients per list). The GP will review the list and exclude those women who meet exclusion criteria. The remaining women will be mailed the screening questionnaire together with a letter from their GP endorsing the project, an information sheet, a resource card listing contact numbers for various support agencies and a reply paid envelope. In the survey the respondents are told that the **weave **team is trying to work out ways to improve the care women receive in general practice, and particularly in relation to emotional well-being. At the end of the screening survey, respondents are asked if they would like to hear more about **weave**, the next stage of which involves "completing a survey about relationship and emotional issues (e.g. depression, domestic violence, stress or worry)." A reminder is mailed out from the practice to all women 14 days following mail-out of the screening survey.

Eligible women will be phoned by a research assistant who will explain the nature of the study (a project looking at ways of improving the care women receive from their GP when they are experiencing relationship and emotional issues, such as being afraid of your partner or ex-partner). It will be explained that the project will involve three surveys over approximately 18 months and that they may or may not be invited to see the GP to discuss relationship and emotional issues depending on the group in which they are placed by chance. Those eligible and agreeing to be involved are sent a baseline survey, information sheet, resource card and a reply paid envelope. Once the baseline survey and consent form have been returned, women are officially enrolled in the trial. A reminder is sent to patients 10 days post baseline survey and a phone call reminder at 20 days. All GPs (and their female patients) in a given wave (there will be four waves) are randomised to intervention or comparison once the cut-off for the return of the baseline survey (30 days following mail-out) for the final GP in the wave has been reached.

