### Sequence generation and allocation concealment

Allocation to intervention or comparison will be based on clusters rather than individuals. The trial will be run in four consecutive overlapping waves. Approximately 10 GPs will be randomised in each wave. Characteristics of GPs, including age, sex, years of general practice experience and knowledge about management of partner abuse, will be measured at baseline to check the extent to which randomisation creates equivalence across the two groups. To promote comparability of the intervention and comparison clusters with respect to cluster characteristics, practitioners will be stratified according to whether they are urban or rural and block randomisation with random block sizes will be used within each stratum. The randomisation will be performed by a statistician not directly involved in the study and who is blinded to the identity of the practitioners. Allocation of clusters to intervention or comparison will done following collection of baseline data. In other words, at the time of screening and recruitment of women, the allocation of GPs (and therefore, of women) will be unknown.

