#### Economic evaluation

The primary economic evaluation will use a cost-consequences analysis, with any incremental costs compared to all incremental outcomes as detailed above. If this does not reveal a dominant result for the cost-effectiveness of the intervention, secondary economic analysis will involve incremental cost-effectiveness analysis using individual outcome measures and cost-utility analysis using SF-12 data. The economic evaluation will be conducted from both a health care and societal perspective, with costs including resources used in intervention delivery and practice-based system change and women's use of health care and other societal resources.

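### Screening is counted as part of the tested intervention, but both arms are screened before randomisation, so the trial cannot estimate its effect on women's outcomes

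*Protocol article*

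**What the plan says.** Three places in the protocol article treat screening as something the trial evaluates.

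- Aims of weave: the primary aim concerns a "multifaceted intervention consisting of screening for intimate partner abuse and feedback for GPs, training for GPs, a brief counselling intervention for women", together with minimal practice organisational change.
- Abstract, Background: the trial is of a "general practice-based intervention consisting of screening for fear of partner with feedback to GPs, training for GPs, brief counselling for women" and organisational change.
- Abstract, Discussion: "It will provide important knowledge about the effectiveness of a brief method of screening, professional IPA training program and brief counselling for women".

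The closing Discussion again pairs screening with counselling when it describes what should be tested.

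The design sections describe a different comparison.

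- Patient recruitment: for each participating GP, after exclusions, "The remaining women will be mailed the screening questionnaire together with a letter from their GP endorsing the project". The mailing also contains a resource card of support agencies.
- Inclusion and exclusion criteria, Women: women are invited into the trial if "they indicate in the screening survey that they have been afraid of their partner or ex-partner in the last 12 months" and they want to hear more about the project.
- Sequence generation and allocation concealment: "at the time of screening and recruitment of women, the allocation of GPs (and therefore, of women) will be unknown".
- Abstract, Methods/Design: after baseline data are collected, GPs are randomised either to training plus inviting women to counselling, or to basic education and usual care.
- Intervention: the intervention is said to have professional, patient and organisational elements. Screening is not among them.

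**The concern.** A randomised comparison gives the effect only of what differs between the arms. Here the screening survey, the recruitment call, the baseline survey and the resource card all come before allocation and reach women in both arms. Whatever benefit or harm they bring is common to both arms and drops out of the difference.

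The stated aim and the abstract's conclusion therefore promise more than the comparison can deliver. The Screening section of the Background describes a Canadian trial that compared screening with usual care on women's health outcomes. A reader could set this trial's result beside that one, citing a positive result as evidence that screening works or a null result as evidence that it does not. Neither inference would rest on a randomised comparison.

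There is also an internal contradiction: screening is a component in the abstract and the aims, but not in the section that defines the intervention.

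**Working it through.** **1. The plan's own figures reproduce, and the point does not touch them.** Inputs are from Number of participants required and Table 1: 89 women per arm at 12 months, 20 GPs per arm, intra-cluster correlation 0.02, two-sided 5%, a difference of 0.5 SD, and 10% versus 40% for having a safety plan.

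- Unclustered size for 0.5 SD at 80% power: 63 per arm.
- Design effect with m = 89/20 = 4.45: 1 + (4.45 − 1) × 0.02 = 1.069. Required: 63 × 1.069 = 67.3, so 68 per arm.
- Power with 89 per arm: effective size 89/1.069 = 83.3, power 0.897. With m = 268/40 = 6.7 the design effect is 1.114, the effective size 79.9 and the power 0.885.
- Safety plan: 32 per arm needed unclustered; power at effective size 83.3 is 0.996.
- Funnel: 20,000 × 0.40 × 0.10 × 0.60 × 0.70 × 0.80 = 268.8, given as 268. Two thirds of 268, halved, is 89.3.

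The claim of at least 80% power holds.

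**2. Exposure by arm.**

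| Element | Intervention arm | Comparison arm |
|---|---|---|
| Mailed the screen | about 10,000 (20 GPs × 500) | about 10,000 (20 GPs × 500) |
| Trial entrants, all screen-positive | about 134 | about 134 |
| Entrants not screened | 0 | 0 |
| Resource card, recruitment call, baseline survey | yes | yes |
| Healthy Relationships training of the GP | yes | no (basic education; a workshop is offered after the trial) |
| Invitation to counselling | yes | no |
| Organisational change | yes | not described |
| Feedback of screen result to the GP | implied by the GP's invitation letter | not stated |

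**3. What the difference estimates.** Write S for screening, R for the response that follows it, and Y(S, R) for the mean outcome.

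- Effect named in the aim, screening included: Y(1,1) − Y(0,0).
- Effect randomised: Y(1,1) − Y(1,0), in women who screened positive, consented and returned a baseline survey.
- The gap between them: Y(1,0) − Y(0,0), the effect of screening followed by usual care.

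No woman in the trial has S = 0, so that last term cannot be estimated, whatever the sample size or the analysis model.

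**4. Cost of screening, if it counts as part of the package.** Mailed surveys per entrant: 20,000/268 = 74.6. For the intervention arm alone: 10,000/134 = 74.6. With about the same number mailed in each arm, a plain between-arm cost difference removes this item.

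**The case against.** The strongest reply is that the comparison is disclosed and well chosen. The abstract's Methods/Design section gives both arms and the order of events, the hypothesis under Aims of weave rests on the counselling, and the aim is worded for a package without promising to isolate screening. Screening before allocation also protects a cluster trial from recruitment bias. All of this is right, and the design should stay. But the package including screening is never compared with care without it, and the abstract's Discussion names screening as one of three things whose effectiveness will be informed.

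That phrase could be read as how well the method works in practice, since acceptability and harm are measured (Trial phase). That reading is possible. It argues for descriptive wording, because yield and acceptability are not an effect on outcomes.

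A reader might infer more than the document supports:

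- *That the results have no bearing on screening policy.* The Screening section gives the lack of an effective treatment after identification as a major unmet criterion. A trial of treatment in screen-positive women addresses that directly, although it does not estimate a screening effect.
- *That feedback to GPs is part of the randomised difference.* The invitation letter implies it for the intervention arm; nothing says what comparison GPs are told.
- *That the economic evaluation leaves screening out.* The plan compares "any incremental costs compared to all incremental outcomes as detailed above" and does not say how screening costs are assigned, a detail an article may leave to the fuller plan. The point is conditional.
- *That about 149 surveys are needed per intervention woman.* That divides both arms' 20,000 mailings by one arm's 134 women. The like-for-like figure is about 75.

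**Conclusion.** The aim and the abstract's conclusion are wrong as written. The trial gives no randomised information on the effect of screening on women's outcomes, because exposure to it is the same in both arms and there is no unscreened comparator. The definition of the intervention in the abstract and the aims contradicts the one in the Intervention section, and the two must be reconciled.

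This rests on the recruitment sequence as the article describes it and does not depend on any numerical assumption. The figure of about 75 mailed surveys per entrant assumes the plan's own funnel and matters only if screening is costed as part of the package. The conclusion is firm for screening and open for feedback to GPs. The fault lies in what the trial says it will show: the design, sample size and stated power are unaffected.

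**What to change.** 1. Reword the primary aim, the abstract and the planned conclusion as the effect of GP training, invited brief counselling and minimal organisational change, compared with basic education and usual care, among consenting women who screened positive for fear of a partner or ex-partner in the last 12 months.
2. State whether comparison GPs are told which of their patients screened positive. Name feedback as part of the tested intervention only if it differs between the arms.
3. Remove the claim to evaluate the effectiveness of screening. Report its response rate, yield, acceptability and harm descriptively.
4. Use one definition of the intervention throughout, consistent with the Intervention section.
5. If screening stays in the package for the economic evaluation, note that a plain between-arm difference cancels its cost, and report that cost separately.

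The cost is a change of wording and, under item 5, one further cost line. The downside is a narrower claim. A claim about screening itself would need an unscreened comparison group, which this trial does not have.
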